## Data collection

### Clinical variables

Data collection is based on the standardised COCOE multidisciplinary clinical assessment form, adapted for input into REDCap [28,29]. This form captures all relevant clinical information encountered during routine care, including: patient demographics; referral details; primary diagnosis; involvement of subspecialists; current medications and allergies; vaccination status; detailed birth and surgical history; prior hospitalisations; relevant investigations; and multidisciplinary assessments. It also documents gastrointestinal, urological, gynaecological, dietary, developmental, social, and family history, as well as physical examination findings, growth parameters, and care plans. For research purposes, only de-identified data elements required to address the study objectives are abstracted, ensuring no additional procedures or burden beyond routine clinical care.

### Data abstraction procedures and reliability

To ensure consistency of abstraction from the multidisciplinary assessment form, the registry operates under a written data dictionary and standard operating procedure that specify, for every REDCap field, the permitted values, the source document of record, and the rule to be applied when sources disagree. Operative reports and histopathology reports take precedence over clinic correspondence for surgical and diagnostic variables; the multidisciplinary assessment form takes precedence for functional and psycho-social variables. All abstractors complete a standardised training package and must reach at least 90% field-level agreement with the Study Coordinator across five benchmark charts before abstracting independently. REDCap instruments use closed-response fields, branching logic, and range and cross-field validation rules wherever possible, so that free-text entry is reserved for variables that cannot be pre-coded [28,29].

A random 10% sample of records is independently re-abstracted each quarter by a second trained abstractor blinded to the original entry. Agreement will be quantified using Cohen’s kappa for categorical variables and the intra-class correlation coefficient for continuous variables, against a pre-specified acceptability threshold of κ ≥ 0.80 or ICC ≥ 0.80. Fields falling below this threshold will trigger review of the field definition, retraining of abstractors, and re-abstraction of affected records. Reliability statistics will be reported in the first descriptive registry manuscript and at each subsequent annual audit.

Adherence to the protocol is itself treated as a monitored registry metric. The proportion of eligible patients approached, the proportion consented, the proportion of scheduled assessments completed within their pre-specified age window, and instrument-level completion rates are reported quarterly to the registry Director. Pre-specified action thresholds, for example an assessment-window adherence rate below 70% across two consecutive quarters, trigger review of clinic workflow and, where necessary, a protocol amendment. These adherence metrics will be published alongside outcome data so that readers can judge the completeness and fidelity of the underlying datasets.

Variables collected will include: demographic information (parent and child age, sex); Social Determinants of Health (gender, race/ethnicity, income, education, and first three digits of the postal code-based Material and Social Deprivation Index); health services utilisation (emergency room/outpatient visits and inpatient admissions over the past year); clinical data (diagnosis with severity, surgical procedures with dates, prematurity, comorbidities, and complications); and Patient-Reported Outcome and Experience Measure (PROM/PREM) data.

### Social determinants of health

(a) Individual-level variables, collected directly from participants and caregivers using Statistics Canada standard wording [30]: sex assigned at birth (male, female, intersex); gender identity (man/boy, woman/girl, non-binary, another gender identity, prefer not to answer); race/ethnicity (self-identified, using Statistics Canada visible minority and Indigenous identity categories); household income before taxes (six categories: < $20,000; $20,000–$39,999; $40,000–$59,999; $60,000–$79,999; $80,000–$99,999; ≥ $100,000, aligned with Low Income Measure thresholds for Québec); highest level of education completed by the primary caregiver (less than high school diploma; high school diploma or equivalent; post-secondary certificate or diploma; bachelor's degree; graduate or professional degree); and employment status of the primary caregiver. For all individual-level SDOH variables, a “prefer not to answer” option will be provided and treated as missing in analyses, with missingness described and addressed using the plan detailed in the Statistical Analysis section.(b) Area-level deprivation, derived from the Pampalon Material and Social Deprivation Index (MSDI), 2021 census-based [31], linked to participant residence via the first three characters of the postal code (forward sortation area, FSA) using the Statistics Canada Postal Code Conversion File. Material deprivation (a composite of employment, income, and education) and social deprivation (a composite of living alone, separated/widowed/divorced status, and lone-parent status) will be treated as separate dimensions and analysed as quintile scores (Q1 = least deprived to Q5 = most deprived). [32] The FSA will not appear in any publication output.

### Severity and phenotype

For ARM, anatomical and surgical severity will be classified using the Krickenbeck International Classification [33], comprising the following major clinical groups: perineal fistula; rectourethral fistula (bulbar or prostatic); rectovesical fistula; vestibular fistula; cloaca; no fistula; and rectal atresia/stenosis. For HD, severity will be characterised by length of aganglionosis confirmed by operative report and histopathology, using the following categories: short-segment (rectosigmoid transition zone); long-segment (transition zone beyond the sigmoid colon); total colonic aganglionosis (TCA); and total intestinal aganglionosis (TIA) [34]. Separate structured fields will capture: syndromic status (yes/no; if yes, syndrome name including trisomy 21, VACTERL syndrome association, RET proto-oncogene variants, and other named syndromes); and associated anomalies, documented using a structured checklist covering vertebral, cardiac, tracheo-oesophageal, renal, and limb anomalies (VACTERL) [35], with additional free-text fields for genitourinary, spinal, and other anomalies outside this classification.

### Patient-reported outcomes

During clinic visits or between encounters (online or paper), families are asked to complete validated surveys addressing multiple domains of well-being (Table 3). Surveys are available in English and French. Instruments include the Hirschsprung's and Anorectal Malformation Quality of Life (HAQL) questionnaire (disease-specific symptoms and quality of life, with age-specific and stoma-specific versions) [18]; the Baylor Continence Scale (BCS) [16], evaluating the social and functional impact of continence issues; the PedsQL General Well-being Scale [36]; the PedsQL Family Impact Module [36]; the Parent Experience of Child Illness (PECI) [37]; and, for those in bowel management programmes, the Patient-Reported Experience and Outcome Measures in Bowel Management Programmes (PREOM-BMP) [38]. Both French and English validated versions are available and will be used according to family language preference. Proxy-report by the parent or caregiver will be used for children aged 6–11 years; self-report will be used from age 12 onward, consistent with the validated age thresholds for each version.

**Table 3 pone.0356813.t003:** Summary of patient-reported outcome surveys.

Domain	Scale	Duration	Respondent	Brief description
Disease-specific	HAQL and BFS	10–20 min	Child (older) or Parent	Multiple-choice questions about symptoms and QoL; age-specific versions; stoma-specific items.
Social impact	BCS	10–15 min	Child (older) or Parent	23 questions on social continence and impact on life; self- or proxy-report.
General well-being	PedsQL General Well-being	4–10 min	Child or Parent (proxy)	Flexible item banks and short forms assessing physical, mental, and social health; domains include pain, fatigue, physical function, depression, anxiety, and social function.
Family functioning	PedsQL FIM	10–15 min	Parent	36-item parent-report scale assessing physical, emotional, social, and cognitive functioning, communication, worry, daily activities, and family relationships.
Parental well-being	PECI	10–15 min	Parent	25-item measure of adjustment to caring for a child with chronic illness; covers guilt/worry, unresolved sorrow/anger, long-term uncertainty, and emotional resources.
Family experience	PREOM-BMP	10–15 min	Parent	33-item survey for families of children in bowel management programmes; covers physical/emotional health, QoL, treatment success, financial considerations, schooling, and social concerns.

*BCS, Baylor Continence Scale; FIM, Family Impact Module; HAQL, Hirschsprung's and Anorectal Malformation Quality of Life; PECI, Parent Experience of Child Illness; PREOM-BMP, Patient-Reported Experience and Outcome Measures in Bowel Management Programmes; QoL, quality of life.*

For the purposes of this registry, a bowel management programme is defined as a structured, clinician-supervised regimen of enemas, laxatives, or dietary modification,  prescribed and monitored by the COCOE team,  for the management of fecal incontinence or constipation that has not responded to first-line measures. Eligibility for the PREOM-BMP is determined at each clinic visit by the responsible clinician and recorded in REDCap. Based on current COCOE caseload, approximately 40–50% of enrolled participants are expected to be in a formal bowel management programme at any given assessment visit.

### Survey administration and burden mitigation

The six instruments have a combined estimated completion time of 54–95 minutes depending on age and programme status. To reduce burden, instruments are administered in a staggered fashion across visits: the HAQL, BCS and BFS are prioritised at each visit; the PedsQL modules and PECI are administered at alternating annual visits; and the PREOM-BMP is administered only to eligible families. Where possible, surveys are distributed electronically via REDCap prior to the clinic visit to allow completion at home, reducing in-clinic time. Paper versions are available for families without internet access, and a trained research assistant is available to assist with completion where literacy or language is a barrier. Surveys are available in English and French. In the event of partial completion, available items will be scored according to the instrument's published scoring guidelines; instruments with fewer than the minimum required items completed will be recorded as missing and addressed per the missing data plan in the Statistical Analysis section. Based on experience from comparable paediatric surgical registries, we anticipate an instrument completion rate of approximately 70–80% per visit; completion rates will be reported at each annual analysis.

## Data management

Data are collected at each clinic visit by study team members with approved access to the medical record. Online surveys are created and collected directly in REDCap; paper surveys and telephone surveys are entered by a team member. REDCap (Research Electronic Data Capture) is a secure, web-based platform hosted at the Research Institute of the McGill University Health Centre (RI-MUHC) that provides validated data capture, audit trails, automated export procedures, and data interoperability [28,29].

## Statistical analysis

Analyses are pre-specified by objective as follows.

**Objective 1:** Incidence and clinical outcomes. Descriptive summaries of diagnosis, surgical procedures, and complication rates will be reported using means (SD) or medians (IQR) for continuous variables and frequencies (%) for categorical variables [39]. Time-to-event outcomes (e.g., first HAEC episode, reoperation) will be analysed using Cox proportional hazards regression. Where competing risks are present (e.g., death or transition to adult care prior to the event of interest), the Fine-Gray subdistribution hazard model will be applied [40]. Candidate predictors for each time-to-event model are pre-specified as: diagnosis type, Krickenbeck category or aganglionosis length, age at index repair, sex, syndromic status, and area-level deprivation quintile.

**Objective 2:** Patient-reported outcomes. Longitudinal PROM/PREM data collected across multiple clinic visits will be analysed using linear mixed-effects models (for continuous scores) or generalised estimating equations (GEE; for binary or count outcomes), with an unstructured or autoregressive covariance structure selected by the Akaike Information Criterion [41]. Cross-sectional group comparisons at a single timepoint will use chi-square or Fisher's exact tests (categorical) and independent-samples t-tests or Mann-Whitney U tests (continuous), as appropriate.

**Objective 3:** Factors associated with key outcomes. Time to achievement of fecal continence will be estimated using the Kaplan–Meier method, with curves reported separately for ARM and HD given the use of disease-specific instruments. Given the embryological, surgical, and prognostic distinctions between the two conditions, and the use of disease-specific continence instruments, multivariable analyses will be conducted separately for ARM and HD rather than as a single combined model. For each disease cohort, a Cox proportional hazards model will be fitted with disease-appropriate pre-specified candidate predictors: for ARM, Krickenbeck category, age at index repair, sex, syndromic status, and area-level deprivation quintile; for HD, length of aganglionosis, age at index repair, sex, syndromic status, and area-level deprivation quintile. The proportional hazards assumption will be tested for each model using Schoenfeld residuals. Where competing risks are present (death or transition prior to the continence event), the Fine-Gray subdistribution hazard model will be applied within each cohort. Pre-specified landmark analyses will report the proportions achieving continence by age 5 and age 10 for each disease, to allow benchmarking against published ARM and HD cohort data. For each disease-specific model, multivariable Cox regression will be triggered only once the events-per-variable (EPV) threshold of 10 is met within that cohort at interim review; otherwise analyses for that cohort will be limited to descriptive and unadjusted comparisons.

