The primary outcome is time to achievement of fecal continence from the date of definitive surgical repair, analysed as a time-to-event outcome. For participants with ARM, continence is assessed using the Baylor Continence Scale (BCS) [16], with social continence defined as no soiling episodes in the preceding 4 weeks per published BCS criteria, completed by the parent or caregiver proxy up to age 11 and by self-report from age 12. For participants with HD, continence is assessed using the Bowel Function Score (BFS) [17], with social continence defined as a BFS score ≥ 17, administered to the parent or caregiver proxy up to age 11 and by self-report from age 12. Both instruments are administered at every annual clinic visit beginning at age 3 years. The earliest clinically meaningful assessment for continence is age 3, consistent with normal developmental milestones for voluntary bowel control. Participants will be censored at age 18, death, transition to adult care, or loss to follow-up, whichever occurs first.

Pre-specified secondary outcomes, listed in priority order, are: (1) Hirschsprung-associated enterocolitis (HAEC), defined as at least one physician-confirmed episode meeting the Ruttenstock diagnostic criteria and requiring medical treatment, assessed at each annual visit [20]; (2) reoperation rate, defined as any unplanned surgical return to the operating room following index repair, assessed cumulatively; (3) disease-specific quality of life, measured using the HAQL [18] at ages 6, 10, and 14 years using age-appropriate versions; (4) transition readiness, assessed at ages 14 and 17 years using the validated Transition Readiness Assessment Questionnaire (TRAQ) [19], and (5) loss to follow-up rate, defined operationally in the Loss to Follow-Up section. Each secondary outcome will be reported descriptively and, where the events-per-variable threshold is met (see Sample Size section), included as an endpoint in pre-specified multivariable analyses with the analytic role specified in the Statistical Analysis section.

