Combining HD and ARM within a single registry carries both operational and analytic risks. Operationally, the two cohorts share only part of the data model. Shared elements (demographics, social determinants of health, health service utilisation, PedsQL modules, PECI, PREOM-BMP, TRAQ, and the loss-to-follow-up definition) are captured on common forms, while disease-specific elements (Krickenbeck classification and the BCS for ARM; length of aganglionosis, HAEC ascertainment, and the BFS for HD) are captured on separate branching instruments, so that no clinician or abstractor is presented with a field that does not apply to the patient in front of them. Analytically, the two cohorts are never pooled for primary, survival, or multivariable analysis, and the events-per-variable threshold is assessed within each cohort separately. This is a conservative choice that may delay adjusted analyses in the smaller HD cohort. Pooling is confined to descriptive summaries of registry-level metrics such as enrollment, data completeness, and loss to follow-up, where disease group will always be reported as a stratifying variable. The main residual risk is therefore loss of statistical efficiency rather than confounding, and it is accepted in preference to a single combined model whose coefficients would be difficult to interpret clinically.

Finally, the primary outcome relies on instruments administered by proxy in younger children and by self-report from age 12, so the change of respondent within an individual’s follow-up may introduce measurement discontinuity. Respondent type will be included as a covariate in longitudinal models, and the pre-specified landmark estimates at ages 5 and 10 fall wholly within the proxy-report period, allowing an interpretation that is unaffected by the transition to self-report.

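### Unadjusted two-sample tests for cross-sectional patient-reported outcomes can mix age and respondent effects into group differences when the timepoint is a visit rather than a fixed age

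*Protocol article*

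**What the plan says.** The Statistical analysis section, Objective 2, gives two methods for patient-reported outcomes (PROs).

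- Repeated data: "Longitudinal PROM/PREM data collected across multiple clinic visits will be analysed using linear mixed-effects models (for continuous scores) or generalised estimating equations".
- Single-timepoint data: "Cross-sectional group comparisons at a single timepoint will use chi-square" or Fisher tests for categorical scores, and t or Mann-Whitney tests for continuous ones. No covariate, age band or respondent stratum is attached, and neither the groups nor the timepoint is defined.

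Other sections bear on this:

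- **Respondent.** Patient-reported outcomes: "Proxy-report by the parent or caregiver will be used for children aged 6–11 years; self-report will be used from age 12 onward". The Outcome measures section sets the same switch at 12 for the BCS and BFS.
- **Recognition of the problem.** Strengths and limitations accepts that the change of respondent may disturb measurement, and answers: "Respondent type will be included as a covariate in longitudinal models". It adds that the continence landmarks at ages 5 and 10 lie within the proxy period.
- **Timing by age.** The HAQL as a secondary outcome is "measured using the HAQL [18] at ages 6, 10, and 14 years using age-appropriate versions"; the TRAQ is set at 14 and 17.
- **Timing by visit.** Survey administration and burden mitigation: "the PedsQL modules and PECI are administered at alternating annual visits". The same section gives the HAQL, BCS and BFS priority at every visit, which does not match the fixed HAQL ages.
- **Entry.** Children are eligible from 0 to 17 years (Study population and setting).

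**The concern.** None of the named tests can separate a group effect from a difference in age or respondent. Because respondent is set by age, a group with more children aged 12 or over is also a group with more self-reports. The protocol treats that switch as a possible source of measurement error, but its two remedies (the covariate in longitudinal models and the continence landmarks) do not reach the cross-sectional tests.

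At stake is the reading of PRO tables that compare groups at one visit or one data cut. A difference could be taken as an effect of the grouping variable when it partly reflects how old the children were and who filled in the form. Such a bias does not shrink as the registry grows, so the chance of a spurious significant result rises with enrolment.

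**Working it through.** **Step 1: which comparisons are exposed.** Set the instrument schedules beside the respondent rule:

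- HAQL at 6, 10 or 14, and TRAQ at 14 or 17: at any one of these ages, every group has the same nominal age and the same respondent type. Essentially unaffected.
- PedsQL General Well-being: scheduled by visit, child or proxy. Exposed to both age and respondent.
- BCS and BFS: annual from age 3, with a switch at 12. Exposed to both if compared by visit across ages.
- HAQL: exposed to both if the every-visit schedule is followed and forms are compared by visit.
- PedsQL Family Impact Module, PECI and PREOM-BMP: parent-report only (Table 3). Exposed to age only.

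**Step 2: formulas.** The protocol gives no figure for these comparisons, so there is none to reproduce. All sizes below are assumptions. With no true group effect and SD = 1:

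- bias b = (gap in mean age × slope per year) + (gap in self-report share × proxy-self difference)
- se = √(2/n), with n per group
- false-positive rate of a two-sided 5% test = Φ(b/se − 1.96) + Φ(−b/se − 1.96)

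This gives se = 0.200 at n = 50 and 0.141 at n = 100.

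**Step 3: age and respondent together.** Assumed ranges: age gap 2 to 4 years, slope 0.03 to 0.05 SD per year, self-report gap 15 to 25 points, proxy-self difference 0.2 to 0.3 SD.

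- No imbalance: b = 0, rate 5.0%.
- Low end: b = 2 × 0.03 + 0.15 × 0.2 = 0.06 + 0.03 = 0.09 SD. Rate about 7% at n = 50 and 10% at n = 100.
- High end: b = 4 × 0.05 + 0.25 × 0.3 = 0.20 + 0.075 = 0.275 SD. Rate about 28% at n = 50 and 49% at n = 100.

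**Step 4: parent-only instruments (age term only).** b = 0.06 to 0.20 SD. Rate about 6% to 17% at n = 50 and 7% to 29% at n = 100.

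**Step 5: respondent term only, other assumptions.** Self-report gaps of 10, 20 and 30 points at n = 100:

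- proxy-self difference 0.2 SD: rates from 5.2% to 7.1%
- 0.5 SD: b = 0.05, 0.10, 0.15; rates 6.4%, 10.9%, 18.6%
- 0.8 SD: rates from 8.7% to 39.6%

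At n = 50 the range over all nine cases is 5.1% to 22.4%.

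The result depends on how the timepoint is defined and on imbalances that the protocol does not state. Steps 3 and 4 also give both effects the same sign; opposite signs would partly cancel.

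**The case against.** The strongest defence is that this is a condensed article, that the covariates of simple descriptive comparisons are usually left to an analysis plan, and that mixed models and GEE are the stated method for repeated PRO data. The PROs listed as secondary outcomes, HAQL and TRAQ, are scheduled at fixed ages where the problem all but vanishes. Three of the four visit-scheduled or programme-based instruments (Family Impact Module, PECI, PREOM-BMP) have only parent respondents. All of that stands and keeps the point minor. It does not remove it: the section presents its analyses as pre-specified and names the tests, so adding adjustment later would change the text rather than fill a gap.

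Stronger readings are tempting but not supported:

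- A reader might infer that the compared groups will differ in age and respondent. The protocol defines neither groups nor timepoint. Incident and previously diagnosed children plausibly differ in age, and so may children in and out of bowel management programmes, but no section says PROs will be compared along those lines.
- A reader might infer that these tests are the only place where age goes uncorrected. Objective 2 names no age covariate for the mixed models or GEE either. The contrast the document supports concerns respondent type.
- A reader might infer that cross-sectional tables will make up much of the early reporting. The milestones place a descriptive manuscript in Year 2 but do not say what PRO comparisons it will contain.

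**Conclusion.** The point holds in limited form. For comparisons defined by visit or calendar date, the stated tests can report age and, where the respondent varies, proxy-versus-self differences as group differences, and the protocol's respondent adjustment does not reach them. Fixed-age comparisons are essentially safe.

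The size cannot be fixed from the document. Under the illustrative inputs the bias runs from 0 with no imbalance to about 0.28 SD, and the false-positive rate from 5% to about 28% at 50 per group or 49% at 100 per group. The upper figures require both imbalances to be at the high end of the assumed ranges and to act in the same direction. This is a worthwhile improvement to the analysis wording and does not touch the primary outcome analysis.

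**What to change.** In the Statistical analysis section, Objective 2:

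1. State whether a single timepoint means an age or a visit.
2. For visit-defined contrasts, use linear regression (logistic or ordinal for categorical scores) within each disease cohort, adjusted for age at completion and, where it varies, respondent type. Comparing within age band and respondent type is an acceptable alternative. Age and respondent are closely tied because of the switch at 12, but the group contrast does not require their effects to be told apart.
3. Add severity (Krickenbeck category or aganglionosis length) as a covariate only when severity is not the group being compared; otherwise the adjustment would remove the contrast of interest.
4. Keep the two-sample tests for fixed-age comparisons and for cells too small to model, labelled as unadjusted.
5. Reconcile the HAQL timing in Survey administration and burden mitigation with the fixed ages in Outcome measures and Table 2.

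The cost is a few degrees of freedom and slightly more analysis work. No new data are needed: birth dates are collected, severity is classified, and respondent type must be recorded already for the longitudinal models.

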## Methods and analysis

### Study design

This study follows a longitudinal, prospective observational design. The registry has no anticipated completion date; patients are recruited on a continuous basis and followed until they reach 18 years of age. Fig 1 summarises the registry workflow, from identification of eligible patients through consent and baseline data capture to the schedule of longitudinal follow-up assessments and the definitions applied at censoring.

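### Transition to adult care is a censoring event in one section and a Fine-Gray competing event in others; it only ends observation and should be censoring throughout

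*Protocol article*

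**What the plan says.** The Protocol article gives two rules for the same outcome.

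- **Outcome measures**, on time to continence: "Participants will be censored at age 18, death, transition to adult care, or loss to follow-up, whichever occurs first". The sentence is not limited to one model.
- **Statistical analysis, Objective 3**, on the same outcome: "Where competing risks are present (death or transition prior to the continence event), the Fine-Gray subdistribution hazard model will be applied within each cohort".
- **Statistical analysis, Objective 1**, on outcomes such as first enterocolitis episode and reoperation: "Where competing risks are present (e.g., death or transition to adult care prior to the event of interest), the Fine-Gray subdistribution hazard model" is to be used.

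Table 2 lists Kaplan-Meier, Cox and Fine-Gray for the primary outcome without saying which events compete.

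Three other features matter. The clock measures "time to achievement of fecal continence from the date of definitive surgical repair". Under Study design, "patients are recruited on a continuous basis and followed until they reach 18 years of age". Age at repair is a pre-specified predictor in both disease models: "for ARM, Krickenbeck category, age at index repair, sex, syndromic status, and area-level deprivation quintile"; and "for HD, length of aganglionosis, age at index repair, sex, syndromic status, and area-level deprivation quintile".

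**The concern.** A competing event makes the outcome impossible. Death does that. Transition does not: a child can still become continent, have enterocolitis or be reoperated on after leaving paediatric care, but the registry no longer sees it. Reaching age 18 ends observation in the same way and is treated as censoring.

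Two things are at stake. First, Fine-Gray and cumulative-incidence results with transition as competing describe an outcome in which transitioned children never have the event, so late cumulative incidence is too low. Second, time to transition equals age at transition minus age at repair. Children repaired later therefore meet the spurious competing event sooner on the analysis clock, which can pull the coefficient for age at repair downward even when age at repair has no effect. With two rules on the page, the analyst could also choose between two results after seeing them.

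**Working it through.** The protocol gives no figure for this point, so there is none to reproduce.

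**1. The texts side by side.** Outcome measures: age 18, death, transition and loss to follow-up are all censoring. Objectives 1 and 3: death and transition are competing events; age 18 and loss to follow-up are not mentioned. So a child who transitions just before 18 stays in the Fine-Gray risk set as permanently event-free, while one who reaches 18 without transitioning is censored.

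**2. Effect on cumulative incidence.** Illustrative assumptions, none from the protocol: a constant continence hazard h of 0.03 or 0.06 per year from repair, whatever the age at repair; repair at age 4; a share s of event-free children (30% or 90%) transitioning at age 16, which is 12 years after repair. At 14 years after repair the true value is 1 - exp(-14h). With transition as competing it is F(12) + (1 - s) × [F(14) - F(12)], where F(t) = 1 - exp(-ht).

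- h = 0.03: F(12) = 30.2%, F(14) = 34.3%. With s = 30% the estimate is 33.1% (1.2 points low); with s = 90% it is 30.6% (3.7 points low).
- h = 0.06: F(12) = 51.3%, F(14) = 56.8%. With s = 30% the estimate is 55.2% (1.7 points low); with s = 90% it is 51.9% (5.0 points low).

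A child repaired at birth with the same hazard reaches transition only 16 years after repair, so at 14 years there is no shortfall (34.3% or 56.8%). The difference between early and late repair is produced by the rule alone.

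**3. Effect on the regression.** Simulation under a true null for age at repair. Assumptions: 80% repaired in the first year and 20% at ages 1-8; hazard 0.03 or 0.06; 30% or 90% transitioning from age 14 or 16; the rest censored at 18.

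| Handling of transition | Hazard ratio per 5 years later repair |
|---|---|
| Censored, Cox | about 1.00 |
| Competing, Fine-Gray, marginal censoring weights | about 0.7-0.9 |
| Competing, Fine-Gray, child leaves the risk set at the known age-18 time | about 0.87-1.00 |

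The gap between the last two rows has a separate cause: marginal weights ignore that age-18 censoring falls at 18 minus age at repair and so depends on the covariate.

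**4. How far it depends on the setting.** A second null simulation put transition at ages 17-18 for every child still event-free and kept transitioned children in the risk set. False rejection (two-sided 5%) used 340 children, half of the projected upper total of 680, with 39% continent 10 years after repair.

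| Age at repair | False rejection, Cox | False rejection, Fine-Gray |
|---|---|---|
| All in first year | 4.1% | 4.7% |
| 15% at 1-6 years | 5.4% | 10.9% |
| 30% at 1-10 years | 5.4% | 51.2% |
| Uniform 0-10 years | 4.3% | 61.1% |

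With all repairs in the first year the per-year ratio is 0.965-0.981, but the covariate spans only one year, so the largest contrast is 2-4%. At a 5-year data cut the per-year ratio is 0.945-0.982 and Fine-Gray false rejection is 3-9%.

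**5. Start of assessment at age 3.** With continence observable only from age 3 while time runs from repair, the Cox ratio under the null rises to 1.01-1.14 per year. The Fine-Gray estimate then falls on either side of 1, but stays below the Cox estimate in every scenario.

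**The case against.** **The two rules may describe different models.** A cause-specific Cox model does censor competing events, and Table 2 lists Cox and Fine-Gray together. Outcome measures could then describe Kaplan-Meier and Cox, and Objective 3 the Fine-Gray model. This softens the contradiction, but the text does not say it, and Fine-Gray would still count the wrong event. Cumulative incidence of continence before leaving paediatric care is a definable quantity, but the protocol does not say that it wants it.

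**The size is uncertain.** A reader might infer that the plan will make late repair look harmful. The documents do not support that. They give neither the spread of age at repair nor the share and age of transition; ages 14 and 17 are only the timings of the transition-readiness questionnaire. The age-3 start can push the estimate the other way, so the net direction is not established. Nor is the whole shift due to transition: part of it comes from how age-18 censoring is weighted. These points stand.

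**The scheduled outputs are little affected.** At the Year 5 analysis the distortion is small, and the landmarks at ages 5 and 10 precede every transition age assumed here. This stands too, but the registry has no end date and follows children to 18, so the rule matters more as it matures.

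**Transition may not be uninformative.** If its timing depends on bowel function, plain censoring is biased as well. That calls for a sensitivity analysis, not for Fine-Gray, which does not correct informative censoring. The planned censoring weights address loss to follow-up and non-response, not transition.

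**Conclusion.** The point holds as a conflict in the text and a wrongly specified competing event. Transition is both censoring and competing for the primary outcome, no section says which governs, and as a competing event it makes Fine-Gray treat transitioned children as never having the event. That this lowers late cumulative incidence follows from the definition: 1 to 5 points in the worked example.

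The downward pull on age at index repair is a possible consequence of uncertain size. Under a true null with 20% of repairs at ages 1-8, the subdistribution hazard ratio per 5 years is about 0.7-0.9 with marginal weights and about 0.87-1.00 with the known age-18 time. It is near nil if almost all repairs are in infancy and small at Year 5. The lower figures should not be read as a forecast for this registry.

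**What to change.** State one rule for all time-to-event outcomes: death is the only competing event in Fine-Gray and cumulative-incidence analyses, and is censored only in the cause-specific Cox model; transition to adult care and age 18 are censoring. Remove transition from the competing-risk clauses under Objectives 1 and 3, and align Table 2 and the censoring sentence in Outcome measures.

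Extend the inverse-probability-of-censoring sensitivity analysis already planned under Missing data to transition. The predictors listed there contain no measure of bowel function, so the most recent continence score should be added for this purpose.

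The cost is wording in a few places and one extension of a planned sensitivity analysis. No new data are needed, and the protocol reports that no formal analysis has yet been done, so the change can still be made before any results are seen.
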